**Main secondary**			
Recovery	Composite: absence of bipedal oedema and a MUAC > 125 mm for two consecutive weeks, a 4-week minimum duration of RUTF treatment, and a good clinical health (without fever)	Proportion	Throughout the 6-month follow-up period
**Secondary**^a^			
Cost-effectiveness	Incremental cost-effectiveness ratio (ICER)	Ratio	Throughout the 6-month follow-up period
Consumption of RUTF per children with a favourable outcome	Sachets of RUTF consumed	Mean	6-month post-inclusion
Consumption of RUTF per recovered children	Sachets of RUTF consumed	Mean	End of RUTF treatment initiated at inclusion
Average daily weight gain in SAM children recovered	g/kg/day	Daily	End of RUTF treatment initiated at inclusion
Average daily MUAC gain in SAM children recovered	mm/day	Daily	End of RUTF treatment initiated at inclusion
Hospitalisation	Children with at least one episode of hospitalisation	Proportion	Throughout the 6-month follow-up period
Relapse to a new episode	Children with MUAC < 125 or WHZ < − 3 *Z*-score or oedema after RUTF treatment	Proportion	After recovering from the first episode of acute malnutrition
Non-response	Children who did not reach the recovery criteria	Proportion	16 weeks after inclusion
WaST	Children associated with severe and moderate stunting with acute malnutrition	Proportion	Throughout the 6-month follow-up period

^a^All the secondary outcomes will be analysed for the overall population (MUAC < 125 mm or WHZ < − 3 or oedema) and for the secondary populations (SAM WHO and MUAC < 115 mm or oedema)

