### Sample size

We determined the sample size using an expecting success rate of 68% in each arm for the principal objective and a recovery rate of 82% and 74% for the main secondary objectives #1 and #2, respectively. These hypotheses were based on the results found in the pilot non-comparative cohort study implemented in the Mirriah district in 2019 (Personal communication, 2020). Recovery rates under OptiMA protocol were estimated at 91%, 70%, and 57% for children admitted with a MUAC between 115 and 124 mm and WHZ > − 3, those with SAM according to the WHO definition, and those with MUAC < 115 mm, respectively. In the OptiMA-Niger trial, recovery is defined throughout the 6-month follow-up which will increase these estimations. After having been discharged from this study, non-responders and a sample of recovered children were also seen 6 months after their exit in order to estimate a relapse rate. We estimated that children will be followed up on average 4 months after discharge with a relapse rate of 30%.

To demonstrate non-inferiority of the OptiMA or ComPAS strategies with standard protocol, we assumed a non-inferiority margin of 10%, the same as in other non-inferiority trials assessing simplified protocol [11, 13]. We reduced the test significant level (alpha) at 1.25 to consider the multiple testing [17], a power of 90% for the main objective and 80% for the 2 main secondary objectives were applied, and an inflation rate of 5% was used to account for unexploitable data. Calculations were performed using the SAS software (Proc Power TwoSampleFreq). For the principal objective, 568 children are required per arm, and 295 and 384 children per arm for the main secondary objectives #1 and #2, respectively.

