### Follow-up

Table 3 summarises participants’ follow-up during the trial. All participants are monitored for a 6-month period post-randomisation. During the treatment phase, all children are followed once a week in outpatient consultations in each arm. On discharge from treatment, or immediately after inclusion for MAM children aged over 2 years in the standard arm, children are consulted once a month at home until the 6 months post-inclusion is completed. During village visits, a nurse research officer assisted by one or two CHWs monitored the anthropometric and clinical status of these children, referring any child who needed nutritional or medical care to either the primary healthcare facility or to the Mirriah hospital.

**Table 3 Tab3:** Schedule of enrolment, interventions, and assessments, OptiMA Niger

	Admission	Outpatient follow-up	Home visits	6-month post randomisation
Timeline	d0	4–16 weeks^1^	2–5 months^2^	
Frequency	Day	Weekly	Monthly	

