**Assessments**				
Nutritional and medical assessment	x	x	x	x
Hospitalisation if required		x	x	x
Adverse event		x	x	x

^1^Minimum of 4 weeks of RUTF supplementation and a maximum of 16 weeks for the first episode of AM and if relapse

^2^After discharge from the outpatient visit or for children not eligible for supplementation (standard arm aged 24–59 months with a MUAC 115–124 mm and WHZ > − 3 and no oedema)

^3^At the discharge outpatient visit

Failure to reach recovery criteria is defined after 16 weeks in the programme, then children are discharged from OTF as non-responders and consulted once a month at home until they reach the 6-month post-inclusion. For each non-responder discharged with a MUAC < 115 mm, a medical committee meets to decide on the medical follow-up of the child in the trial. Defaulters are defined as a child absent for 3 consecutive visits. CHWs trace children who are absent to motivate caretakers to return to the health facilities. If caretaker refuse to return to the health centre, the child is followed up once a month at home until the 6-month post inclusion period. When caretakers refuse the follow-up at home, the exit status of children is declared “confirmed defaulter” when the vital status is known and “lost to follow-up” when the vital status is unknown.

Children are discharged from outpatient treatment according to the anthropometric exit criteria of their allocation arm. In standard protocol, children need to achieve a MUAC ≥ 125 mm and a WHZ ≥ − 2 without oedema for two consecutive weeks while in OptiMA and ComPAS strategies, children will be discharged if they reach a MUAC ≥ 125 mm without oedema for two consecutive weeks. For each arm, all children will have to participate a minimum of 4 weeks in the programme with good clinical health (absence of fever) to be discharged from the OTF.

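### Relapse is set as a proportion with no fixed window, so arms with different discharge rules can differ in time at risk and show a difference at equal monthly risk

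*Protocol article*

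**What the plan says.** In Table 1 the relapse row gives the event as low MUAC, low WHZ "or oedema after RUTF treatment", the aggregation as a proportion, and the time point as "After recovering from the first episode of acute malnutrition". No length of observation is attached. The next row, non-response, does have one (16 weeks after inclusion). The Objectives list relapse among the outcomes to be compared between the three arms.

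The Follow-up section sets the other end of the interval: "All participants are monitored for a 6-month period post-randomisation". It also says: "Children are discharged from outpatient treatment according to the anthropometric exit criteria of their allocation arm". In OptiMA and ComPAS, "children will be discharged if they reach a MUAC ≥ 125 mm without oedema for two consecutive weeks"; the standard arm needs this and also WHZ ≥ −2. The footnote to Table 3 gives the range of treatment length: "Minimum of 4 weeks of RUTF supplementation and a maximum of 16 weeks for the first episode of AM and if relapse". The Sample size section supplies the planning figure: "We estimated that children will be followed up on average 4 months after discharge with a relapse rate of 30" per cent.

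The Statistical analysis section names Kaplan-Meier, log-rank and proportional hazards methods for time-delay variables, but does not assign relapse to that class.

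**The concern.** If relapse is counted from the end of treatment and observation ends at a fixed date from randomisation, a child's time at risk is 6 months minus time on treatment. A child with MUAC ≥ 125 mm and WHZ between −3 and −2 may leave treatment in a simplified arm and begin to be at risk. On the same growth course in the standard arm, that child is still being treated. A proportion among recovered children then mixes the risk of relapse with the length of observation.

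Relapse is a natural safety question for reduced-ration strategies, and the Discussion gives capturing relapse as a reason for the 6-month follow-up. A difference produced by timing could be read as harm from the simplified strategies. If the timing runs the other way, it could hide harm.

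**Working it through.** **Inputs from the article.** Relapse of 30% over a mean of 4 months after discharge (Sample size); treatment of 4 to 16 weeks (Table 3 footnote); follow-up of 6 months, about 26 weeks (Follow-up).

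**Assumptions, not in the article.** A constant relapse hazard, equal in all arms; a gap of D weeks in discharge; the share of standard-arm children delayed; 300 to 460 recovered children per arm. A month is 52/12 = 4.33 weeks.

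**Step 1: time at risk under the plan's own limits.** Discharge at week 4 leaves 6 − 4/4.33 = 5.1 months. Discharge at week 16 leaves 6 − 16/4.33 = 2.3 months. This agrees with the 2–5 months of home visits in Table 3, so time at risk varies about twofold between children.

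**Step 2: hazard.** h = −ln(0.70)/4 = 0.0892 per month. Check: 1 − exp(−0.0892 × 4) = 30.0%, the planning figure. At the two extremes of Step 1 the same hazard gives 36.4% and 18.6%.

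**Step 3: gap between arms with no true difference.** The simplified arm has 4 months at risk and shows 30.0%. The standard arm shows 1 − exp(−h(4 − D/4.33)).

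| D (weeks later) | Standard arm, all delayed | Spurious gap, all delayed | Spurious gap, half delayed |
|---|---|---|---|
| 2 | 27.1% | 2.9 points | 1.5 points |
| 4 | 24.0% | 6.0 points | 3.0 points |

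The last column averages 30.0% with the delayed figure; for D = 4, (30.0 + 24.0)/2 = 27.0%. If the simplified arms were the ones discharged later, the same gaps would appear with the sign reversed.

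**Step 4: chance of a misleading test.** With a two-sided 5% comparison of two proportions and 300 to 460 recovered children per arm, 30.0% against 24.0% gives a nominally significant excess in the simplified arm with probability 38% to 54%. For 30.0% against 27.0% it is 13% to 17%. The nominal rate in that direction is 2.5%.

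**Step 5: what window is covered.** After a 16-week treatment, 26 − 16 = 10 weeks remain. An 8-week window from end of treatment fits; a 12-week window does not.

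**The case against.** A reader might infer that the plan will show more relapse under the simplified strategies. The documents do not support that.

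- The tapered ration could slow MUAC gain and postpone exit. The Introduction reports that 34.1% of children admitted with MUAC < 115 mm in the Niger OptiMA pilot had not met exit criteria after 10 weeks.
- Standard-arm children aged 24–59 months with MUAC 115–124 mm, WHZ > −3 and no oedema go straight to home visits without supplementation. They have no treatment exit to be delayed.
- The WHZ criterion holds back only children whose WHZ lags behind MUAC, and that share is not given.

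These points stand. They make the direction uncertain, but they do not equalise time at risk.

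The time origin is also open. Under Study outcomes, recovery is defined identically in each arm for the two main secondary populations, with no WHZ term. If relapse is counted from that point, the extra exit criterion does not shorten the standard arm's time at risk. But Table 2 labels the arm-specific criteria as the recovery definition, and the relapse row counts events after RUTF treatment. Neither reading is fixed, and a start after RUTF treatment does not fit standard-arm children who receive RUSF or nothing.

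Finally, the choice of estimator for a lesser secondary outcome usually belongs in the analysis plan, which is not shown. Table 1 does, however, state an aggregation and a time point. Those entries are what need changing.

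**Conclusion.** The point holds in conditional form. As Table 1 is written, time at risk for relapse can differ between arms, and the proportion could show a difference when the monthly risk is equal. The exit rule taken alone points towards more apparent relapse in the simplified arms; the net direction cannot be settled from the article. The spurious gap is 2.9 to 6.0 points if all standard-arm children leave 2 to 4 weeks later, and 1.5 to 3.0 points if half do. Both ranges rest on assumed gaps and a constant hazard.

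The consequence is limited. Relapse is one of several other secondary outcomes, analysed only if non-inferiority is shown on the two main outcomes. A reader might extend the point to the primary outcome, but that composite counts further episodes over a fixed 6 months from randomisation and does not depend on the date of discharge. This is a worthwhile refinement, not a threat to the trial's main conclusion.

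**What to change.** In the relapse row of Table 1, replace the proportion with cumulative incidence of relapse.

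- **Time origin:** one origin, defined the same way in all arms. State whether it is recovery as defined under Study outcomes or end of treatment, and what applies to standard-arm children with moderate malnutrition who receive RUSF or no supplement.
- **Estimator:** the Kaplan-Meier approach already named, censored at the end of follow-up, with death as a competing event (a cumulative incidence estimator, which reduces to one minus Kaplan-Meier when there are no deaths).
- **Comparison:** between arms at a fixed time that the 16-week treatment limit allows, for example 8 weeks. If the origin is outcome recovery, a few late recoveries found at village visits will have less than 8 weeks and are handled by censoring.

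The proportion of all randomised children who recovered and then relapsed by month 6 may be added as a separate description of the strategies. It does not correct for time at risk, since earlier discharge still leaves longer to relapse.

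The cost is analysis wording only; the weekly and monthly visits already scheduled supply the dates. The small downside is that relapses after the fixed time do not count in the fixed-time comparison, though they remain visible on the curve.

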The Optimsing treatment for Acute Malnutrition (OptiMA) strategy has been developed in a research consortium between humanitarians from the Alliance for International Medical Action (ALIMA) non-governmental organisation and scientists from the French National Institute for Health and Medical Research (Inserm). The OptiMA RUTF ration is calibrated to the child’s degree of wasting based on the combination of MUAC status and weight. Thus, more nutritional feeding is given to the most severely malnourished and then gradually reduced as the child’s MUAC increased. Children with MUAC < 115 mm or oedema receive 175 kcal/kg/day of RUTF. Children with MUAC 115–119 mm, either at admission or during the course of treatment, receive 125 kcal/kg/day of RUTF, and children with MUAC ≥ 120 mm receive 75 kcal/kg/day of RUTF (with a minimum of one sachet/day) until discharge from the programme. The OptiMA strategy was first implemented in a proof-of-concept single-arm trial in Burkina Faso in 2018 [10]. The results showed a recovery rate that exceeded SPHERE standards among children admitted with MUAC < 125mm (86.3%; 95% CI 85.4–87.2%) with an excellent health worker adherence to the new RUTF table. However, recovery among children admitted with a MUAC < 115 mm or oedema was poorer than anticipated (70.4%; 95% CI 67.5–73.5%). Then, an individually randomised non-inferiority controlled trial compared the OptiMA strategy to the national protocol was implemented in the Democratic Republic of the Congo (DRC) in 2019 [11]. The OptiMA protocol treated 29% more children with 20% less nutritional inputs compared to the standard protocol. A pilot non-comparative cohort study on 1111 acutely malnourished children per the OptiMA definition was implemented in 2019 in Niger and showed a similar result to the one observed in the above-mentioned study in Burkina Faso with a global recovery rate among children admitted with a MUAC < 125 mm that exceeded 80% ( [10] and Personal communication, 2020). However, recovery among the 290 children admitted with a MUAC < 115 mm remained low (57.7%), partly explained by a high proportion of children (34.1%) not reaching the exit criteria after 10 weeks of participation in the programme (Personal communication, 2020).

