## Objectives

The principal objective aims to determine, 6 months after inclusion, whether the OptiMA strategy or ComPAS strategy leads to a favourable outcome which is non-inferior to what Niger standard protocol, in use in the same outpatient health facilities, provides. The definition of a favourable outcome is described in the “Study outcomes” section.

Two main secondary objectives for this trial are as follows. The first one is to determine whether the recovery rate of children with uncomplicated SAM according to the current WHO definition [14] (e.g. MUAC < 115 mm or WHZ < − 3 or bilateral oedema) managed under the simplified OptiMA or ComPAS strategies is non-inferior to that of the national standard protocol of Niger. The second one is to determine whether the recovery rate of children admitted with MUAC < 115 mm or oedema (+, ++) managed under the simplified OptiMA or ComPAS strategies is non-inferior to that of the national standard protocol of Niger.

Other secondary objectives include description and comparison between the three study arms of the following outcomes: cost-effectiveness analysis, RUTF consumption, relapse after nutritional recovery, non-response after outpatient follow-up, recovery, and success in children who present with both wasting and stunting at inclusion, and to describe the nutritional and clinical status of children hospitalised while enrolled in the study.

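### Non-response at 16 weeks rests on recovery criteria that the article defines in two ways, and one of them is stricter in the control arm only

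*Protocol article*

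**What the plan says.** All places are in the protocol article.

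- **Table 1, Non-response row:** "Children who did not reach the recovery criteria", reported as a proportion at "16 weeks after inclusion". A footnote applies it to the overall population and to the two severe subgroups.
- **Objectives:** the outcome appears among the other secondary objectives as "non-response after outpatient follow-up".
- **Study outcomes and Table 1, Recovery row:** recovery needs the MUAC threshold for two consecutive weeks, no oedema, no fever and at least four weeks of treatment. The text says this holds in each arm. There is no WHZ term.
- **Table 2, Recovery definition row:** the national protocol column requires MUAC ≥ 125 mm and WHZ ≥ −2. The OptiMA and ComPAS columns require MUAC only.
- **Follow-up, discharge:** "Children are discharged from outpatient treatment according to the anthropometric exit criteria of their allocation arm", with WHZ ≥ −2 repeated for the standard arm.
- **Follow-up, exit statuses:** "Failure to reach recovery criteria is defined after 16 weeks in the programme, then children are discharged from OTF as non-responders". Default is a separate status ("Defaulters are defined as a child absent for 3 consecutive visits"), as are confirmed defaulter and lost to follow-up.

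**The concern.** The phrase recovery criteria in the non-response row points to no single definition. Under the study definition the rule is the same in every arm. Under Table 2 and Follow-up, a control child must pass one more test than a child in the other arms. The second set is also the one that produces a recorded status named non-responder, so it is the easy one to analyse.

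If that status is used, part of any difference between arms reflects the rule and not the children. The WHZ term makes the control arm look worse and the reduced-ration arms look better by comparison.

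A second, smaller question is scope. Table 1 taken alone covers everyone not recovered by week 16, whatever the reason. Follow-up describes children who are still in the programme at that point.

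**Working it through.** The article states no expected value for non-response, so there is no figure to reproduce. The sample sizes (568, 295 and 384 per arm) rest on the favourable outcome and on recovery, and they do not enter here. The check is to run example records through each rule.

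| Record | Common study criteria | Exit status under Follow-up |
|---|---|---|
| A. Treated; MUAC ≥ 125 mm from week 6; no oedema or fever; WHZ −2.3 up to week 16 | Recovered, any arm | Control: non-responder. OptiMA, ComPAS: recovered |
| B. Dies at week 3, or defaults at week 5, not recovered | Not recovered; inside the Table 1 wording taken alone | Not a non-responder; other status |
| C. Control, aged 24–59 months, MUAC 115–124 mm, WHZ > −3, no oedema; no supplementation | Cannot meet the four-week treatment criterion | Never in the programme, so never discharged as a non-responder |

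**Record A: direction.** For a treated control child, the exit rule is the common criteria plus WHZ ≥ −2. Meeting the exit rule therefore implies meeting the common criteria, but not the reverse. Let x be the share of control children who meet the common criteria by week 16 but never the WHZ term. Then:

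- control non-response by exit status = control non-response by common criteria + x, with x ≥ 0;
- for OptiMA and ComPAS the corresponding addition is 0.

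The WHZ term thus shifts the comparison by x, in one direction.

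**Record A: size.** The article gives no value for x. If x were 2%, 5% or 10% (an assumption), the shift would be 2, 5 or 10 points. That is 0.02 × 384 ≈ 8, 0.05 × 384 ≈ 19 or 0.10 × 384 ≈ 38 control children in the MUAC < 115 mm comparison. This restates the assumption and is not an estimate. The article does foresee the pattern of adequate MUAC with low WHZ: Eligibility criteria has a rule for WHZ < −3 with MUAC ≥ 125 mm, although those children are not randomised.

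**Record B: scope.** The Introduction reports, for 290 pilot children with MUAC < 115 mm, 57.7% recovered and 34.1% "not reaching the exit criteria after 10 weeks of participation in the programme".

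- Complement of recovery: 100 − 57.7 = 42.3%.
- Gap between the two readings: 42.3 − 34.1 = 8.2 points, or 0.082 × 290 ≈ 24 children.

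This shows that the two readings need not agree. It does not predict the gap in this trial: the pilot was a single-arm OptiMA cohort, the figure is at 10 weeks and not 16, and the article does not say what the 8.2 points consist of.

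**Record C: unsupplemented control children.** The Intervention section and the notes to Table 3 send these children straight to monthly home visits. Taken literally, Table 1 makes all of them non-responders, because they never have four weeks of treatment; the exit status makes none of them so. In the overall population, using the exit status over all randomised children would therefore lower control non-response through this group, against the effect of record A. In the two severe subgroups every control child is treated, so only record A's effect remains.

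**The case against.** The strongest reply is that the Non-response row is shorthand in a condensed article. The Recovery row of the same table is MUAC-based, so a reader may take the criteria from there, and record A is then recovered in every arm. No sentence says the endpoint will come from the field exit status. The article also refers to a separate analysis plan, not shown here, which may settle the derivation. This makes the arm effect conditional. It does not remove the conflict: Table 2 labels the arm-specific set as the recovery definition, and Follow-up uses it to name non-responders.

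Three stronger readings are tempting and are not supported.

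- **Deaths, defaulters and lost children are scored as non-responders.** No passage says so. Follow-up keeps default and loss as separate statuses, and Objectives ties the outcome to outpatient follow-up. Counting such exits as failures would in any case be a defensible convention.
- **Both problems occur together.** They need opposite readings. Counting all exits follows from Table 1 taken literally; the WHZ asymmetry follows from using the exit status instead.
- **Non-response would be overstated by the pilot gap.** That would require 34.1% to be the correct value and to carry over from a 10-week pilot. Neither is established.

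Nor does the article call this outcome a detector of under-treatment. It is listed for description and comparison.

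**Conclusion.** The point holds as an unreconciled definition. Two sets of recovery criteria stand in the article, and the one that governs the non-responder exit status is stricter in the control arm by WHZ ≥ −2. If that status is used, the WHZ term can only raise control non-response, by the share of treated control children with adequate MUAC and WHZ below −2 up to week 16. That share is unknown. The conclusion about direction assumes that the exit rules were applied as written, and it is cleanest in the two severe subgroups. In the overall population, unsupplemented control children pull the other way.

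The scope of non-response with respect to death, default and loss also needs reconciling, but the article fixes no wrong rule there.

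The importance is minor. Non-response is an additional secondary outcome, and Statistical analysis makes the other secondary analyses conditional on non-inferiority for the two main outcomes.

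**What to change.** State in Table 1 or the analysis plan that non-response in every arm means not having met the common criteria of Study outcomes by 16 weeks after inclusion. Derive it from the recorded measurements and not from the field exit status. Say that these criteria apply to the overall population too, since Study outcomes states them only for the two severe subgroups.

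Use all randomised children as denominator. Show death, default and loss to follow-up before recovery as separate categories, so that a reader can form either total.

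Do not require the child to be under treatment at week 16. Control children aged 24–59 months with MUAC 115–124 mm, WHZ > −3 and no oedema receive no supplementation and could then never be non-responders, while the same children in the other arms could. State how this group is classified: either apply the anthropometric and clinical criteria without the treatment-duration term, saying how two consecutive weeks are judged from monthly visits, or report the group separately.

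The cost is a few lines of definition and one derived variable from data already collected. The downside is that control-arm figures will not match routine programme exit statistics. The change concerns outcome classification only and leaves the discharge rules as they are.
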